##### Physical function

Muscle performance will be assessed using four validated tests.

The timed up-and-go test (TUG), which provides a measure of dynamic balance during three commonly performed functional activities: standing up from and sitting down in a chair, walking, and turning [59]. For this test, participants will be seated in a chair (height 45 cm) that will be placed at the end of a marked 3-metre walkway and instructed to stand up, walk at a comfortable speed for 3 meters, turn back to the chair and sit down. To minimise any ceiling effects and make the test more challenging, participants will be instructed to start counting backwards by 3’s from a random number. All participants will be given a practice trial and one test run. A stopwatch will be used to record the time taken (in seconds) to complete the test.

The 4-metre walk test will be used to assess gait speed. Participants will be required to walk in a straight line at their normal walking speed across 4 metres. Participants will begin walking 2 metres prior to and continue walking 2 metres past the 4 metre marker to ensure that a measure of usual walking speed is measured. This test will be recorded using timing gates (Swift Speedlink Performance Equipment systems). Participants will be given one practice trial before completing two test trials. The fastest time (to the nearest millisecond) will be recorded.

The four-square step test (FSST) will be used to assess dynamic standing balance and stepping speed in four different directions [60]. For this test, participants will be asked to step forward, sideways, and backwards over four canes resting flat on the floor in a cross formation as quickly as possible, moving first in a clockwise and then counter-clockwise direction to return to the starting position. After one practice trial, participants will complete two test trials and the fastest time (in seconds) taken to complete the sequence will be measured with a stopwatch and recorded as the final score.

The 30-second sit-to-stand test (STS) is a measure of lower-extremity muscle strength and function and is administered in a chair without arms [61]. Participants start from a seated position in the chair, with arms folded across the chest, and are instructed to stand fully upright and then return to the seated position at their own pace as many times as possible in 30 seconds. The final score will be the number of complete stands recorded during this time.

##### Measures of neural plasticity and voluntary activation

In a subset of approximately 30-40 participants, Transcranial Magnetic Stimulation (TMS) will be used to measure the functional properties of neurons confined to the primary motor cortex and corticospinal pathway, including corticospinal excitability, inhibition and voluntary activation. TMS is a non-invasive, painless and safe technique that is used routinely to investigate the function of the nervous system with very low risk. In this study, single and paired pulse TMS will be applied over the left motor cortex using a BiStim unit attached to two Magstim 200^2^ stimulators (Magstim, Dyfed, UK) to produce motor evoked potentials (MEPs) in the dominant (right) quadriceps. A double-cone coil will be placed over the optimal site of the left primary cortex (sites near the estimated centre of the rectus femoris - approximately 3–4 cm anterior from the vertex) to determine the optimal scalp position that produces the largest MEP amplitude. To ensure all stimuli are delivered to the optimal motor hotspot throughout testing, participants will wear a tightly fitted cap that is marked with a latitude-longitude matrix, positioned with reference to the nasion-inion and interaural lines. All TMS measures will be taken during weak muscle contraction, where participants will be instructed to exert 20 % of their pre-determined maximal voluntary torque (MVC torque), as indicated by a visual line representing voluntary knee extension force on a computer monitor connected to an isokinetic dynamometer (Biodex system 4 Pro, Biodex Medical Systems). The root mean square (rms) of the rectus femoris sEMG will be obtained prior to each TMS stimulus to ensure that there are no changes in pre-stimulus rmsEMG prior to, and following the intervention, which may artificially influence the MEP amplitude. Active motor threshold (AMT) will be determined as the minimum stimulus intensity required to elicit a MEP in the right rectus femoris of at least 200 *u*V in three of five consecutive trials [62]. The stimulus intensity will start at 50 % of maximum stimulator output (MSO) and will be altered in increments of ±1 % of MSO until the appropriate threshold level is achieved.

Single pulse input-output curves will be constructed by stimulating the motor cortex from below each participant’s AMT and by increasing the stimulator intensity by 10 % increments until MEP plateau. From the stimulus response curve, the following parameters will be determined: *MEP*_*Max*_*or peak plateau*, which provides an estimate of the proportion of motoneuron pool that was activated by TMS; *slope steepness*, which provides a measure of the neurophysiological strength of intracortical and corticospinal connections, and *half peak height slope (V*_*50*_*),* which provides a measure of the threshold characteristics of corticospinal cells and alpha motoneurons [63].

Using a paired-pulse technique, we will also measure motor cortex inhibition [short-interval intracortical inhibition (SICI) and long-interval intracortical inhibition (LICI)], which provides a measure of suppression of neuronal firing mediated by γ-amino butyric acid (GABA) receptors [64]. To establish SICI, a conditioning stimulus that is equal to 80 % of AMT will precede a supramaximal test response that will be equal to 120 % of AMT. Each pair of stimuli will be separated by a 3 millisecond interstimulus interval [65]. Similarly, to establish LICI, two supramaximal test responses set at 120 % AMT will be applied to the motor cortex, with each pair of stimuli separated by a 150 millisecond interstimulus interval [66].

Since TMS evokes a muscle twitch as a result of supramaximal stimulation, we will also measure the TMS-evoked twitch force to determine cortical voluntary activation, which provides a measure of the net motor output from the motor cortex to the muscle, as previously described [67]. To establish any changes in cortical voluntary activation, participants will be instructed to match a required force (20 %, 50 %, 75 % and 100 % maximum voluntary contraction) using a horizontal line on a computer screen as visual feedback. During each contraction, TMS will be delivered over the left hemisphere at a stimulus intensity that elicits the largest MEP to evoke superimposed twitches. Cortical voluntary activation will then be calculated using a linear regression as described by Carroll [67].

In order to identify any potential changes in the excitability of the spinal motor neuron pool, maximal electrical responses (M-waves) will be recorded by direct electrical stimulation of the femoral nerve under resting conditions. A Digitimer (Hertfordshire, UK) DS7A constant-current electrical stimulator (pulse duration 1 ms) will be used to deliver each electrical pulse. An increase in current strength will be applied to the femoral nerve until there is no further increase in the amplitude of surface electromyography (sEMG) activity response (M_MAX_) [62].

All MEPs will be recorded via sEMG activity from the right rectus femoris muscle using bipolar Ag–AgCl electrodes. These electrodes will placed on the rectus femoris, three-fifths of the distance between the anterior superior iliac spine and the upper border of the patella, with an inter-electrode distance (centre to centre) of 20 mm [65]. The reference electrode will be placed on the patella to ensure no muscle activity is recorded. All cables will be fastened with tape to prevent movement artefact. The area of electrode placement will be shaven to remove fine hair, rubbed with an abrasive rasp to remove dead skin, and then cleaned with 70 % isopropyl alcohol. sEMG signals will be amplified (1000×), bandpass filtered (high pass at 13 Hz, low pass at 1000 Hz), digitized online at 2 kHz, recorded and analyzed using PowerLab 4/35.

##### Blood pressure

Systolic and diastolic blood pressure will be measured using an automated blood pressure monitor (A&D Instruments, Oxon, UK) after a 5-minute rest period seated in a quiet room. A total of four measurements will be taken with a 2-minute interval between readings; the mean of the final three readings will be used in the analysis.

##### Health-related quality of life

Health-related quality of life (QoL) will be assessed using the Short-Form (SF)-36 (version 2) questionnaire, with permission from the Medical Outcomes Trust (Boston, MA, USA), and reported using Australian norm-based scores according to previously published guidelines [68, 69]. From the 36 items, scores will be calculated for the following eight domains: physical functioning, role-physical, bodily pain, general health, vitality, social functioning, role-emotional and mental health [69]. The data will be normalised to reported data from the 2004 South Australian Health Omnibus survey to allow for appropriate and meaningful comparisons for changes in scores across the eight domains and summary scores [68]. This will allow for the changes in domains to be assessed meaningfully and will account for cultural differences in various populations in regard to the meaning of QoL. Summary measures of the physical and mental components of the survey will be calculated based on a factor analysis of the eight domains among participants in the 2004 South Australian Health Omnibus Survey, resulting in two separate overall summary scores: the physical component summary (PCS) and the mental component summary (MCS) scores [68]. The use of norm-based weights gives each domain score a mean of 50 and a standard deviation (SD) of 10, allowing change in scores to be assessed on a comparable scale.

#### Additional measures

##### Memory, depression and anxiety

The Memory Assessment Questionnaire (MAC-Q) [70] will be used as a measure of subjective memory complaint severity. This tool comprises six questions related to memory functioning in everyday situations in which the participants are asked to compare and rate their current ability compared to when they were aged 40. The total score on the MAC-Q ranges from 7 to 35, where greater scores indicate subjective memory loss. Scores greater than or equal to 25 have been found to be suggestive of age-associated memory impairment.

The Hospital Anxiety and Depression Scale (HADS) questionnaire will be used to measure psychological functioning (anxiety and depression) [71]. The HADS questionnaire is a self-report rating scale consisting of 14 items on a four-point likert scale (range: 0-3 where a higher score represents more severe depression or anxiety), which includes seven questions evaluating cognitive and emotional aspects of anxiety, and seven questions assessing the cognitive and emotional aspects of depression. The results will be reported as the sum of all 14 items, and the sum for each of the two subscales of seven items.

##### Dietary habits

Dietary habits will be assessed from two 24-hour dietary diaries completed by the participants on two consecutive days at baseline and at weeks 4, 8, 12, 16, 20 and 24 and then again at weeks 36 and 48. Participants in the lean red meat group will complete one 24-hour food diary on a day that they consume their red meat and the other 24-hour food diary on a day that they do not consume red meat as part of the intervention. Participants will be required to provide as much detail as possible regarding brand names, cooking methods and recipes for foods and beverages consumed in the past 24 hours. Household measures including measuring cups, plates, bowls and glasses will be used to assist in estimating food portion sizes. Information from these diet history diaries will be checked by the research staff and used to assess total energy and nutrient intakes using Foodworks 7 (Foodworks, Xyris Software, Highgate Hill, Australia).

##### Anthropometry

Height will be measured to the nearest 0.1 cm with a wall-mounted stadiometer and bodyweight to the nearest 0.1 kg using calibrated electronic digital scales.

##### Physical activity

The Community Healthy Activities Model Program for Seniors (CHAMPS) physical activity questionnaire will be used to assess total leisure and recreational physical activity time. This questionnaire has been specifically designed for use in older adults and found to be reliable, valid and sensitive to change [72]. Participants will document their weekly frequency and duration of participation in a ‘typical week’ of the preceding four weeks. The results will be reported as hours per week and, estimated kilojoules per week spent in moderate to high intensity activities.

##### Health and medical history and medication use

A lifestyle questionnaire will be used to obtain information on education background, history of disease(s)/illnesses, falls and fractures, smoking history, current use of medication and dietary supplement use, average weekly alcohol consumption, and weekly television viewing and sitting time, and sun exposure habits. Information on any alterations to, or new, medication prescribed by the participants’ doctor during the study will also be collected by research staff via the monthly phone calls. Information including medication name, dose prescribed, and daily quantity taken will be recorded.

##### Compliance

Exercise cards completed by the participants and monitored by the exercise trainers will be used to monitor adherence to the exercise program. Moreover, at each training session the exercise trainers will document attendance/non-attendance for each participant, and will contact the research staff if participants miss multiple sessions consecutively. The exercise cards will be collected by the research staff from each health and fitness centre at approximately monthly intervals throughout the intervention for review. To monitor the consumption of lean red meat, participants will be asked to record all meat products consumed (from that supplied by the investigators) on a compliance calendar, which will be collected every month. Participants in the carbohydrate control group will also be asked to complete a checklist of carbohydrate-rich meals (pasta and rice) on a daily calendar. Compliance with the vitamin D supplements will be checked by counting returned tablets at after 6 months.

##### Adverse events

At the end of each 4-week period, participants will be required to document any exercise-related adverse events including any injuries related to the exercise program. An adverse event will be defined as an intervention-related event resulting in absence from, or modification to, the exercise program. All exercise-related adverse events forms will be collected monthly so that the researchers can follow-up on any adverse events. Diet-related adverse events (intervention-related events resulting in modification of dietary instructions) will be collected via a telephone administered questionnaire every 8-weeks.

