#### Randomisation and blinding

Randomisation will be at the level of the individual participant in blocks of four, stratified by gender, using a computer-generated random number sequence by an independent researcher. Neither the participants nor research staff involved in the testing will be blinded to the allocation, but those analysing the data will be blinded. A flow diagram of the study protocol is outlined in Fig. 1.

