Depression and anxiety	The Hospital Anxiety and Depression Scale (HADS) questionnaire	x		x		
Diet	24-hour food diaries	Monthly			x	x
Compliance to red meat and carbohydrates	Food records	Daily calendar				
Vitamin D supplement compliance	Pill count			x		
Compliance to exercise program	Exercise cards	Monthly				
Adverse events	Exercise cards and adverse events form	Monthly				

* TMS will also be assessed at week 4 and 8

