#### Secondary outcome measures

Secondary outcome measures to be assessed at baseline and week 24 (unless stated otherwise) will include: changes in fat mass, muscle function, various circulating biochemical, growth, inflammatory and neurotrophic markers, bioavailable zinc, corticospinal excitability and inhibition, blood pressure, blood lipids, memory, mood, anxiety/depression, health-related quality of life and adverse events. Other covariates and variables of interest to be assessed include: anthropometry, habitual physical activity, diet, alcohol intake and smoking status and medication use. A summary of all the outcome measures is shown in Table 1.

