## Discussion

This community-based RCT will be the first to evaluate whether a multi-modal exercise program incorporating PRT in combination with increased dietary protein achieved through the consumption of two ~80 g servings of cooked lean red meat on each of the three training days is a safe and effective strategy to enhance muscle mass, size and strength and cognitive function in community-dwelling older adults. In addition, this study will determine whether such an intervention translates into long-term behavioural changes with regard to adopting a healthier lifestyle that incorporates regular participation in PRT and consumption of a diet high in protein (red meat). This is important because age-related muscle wasting and a decline in cognitive function have both been implicated in the development and progression of many chronic diseases, including falls and dementia. From a public health perspective, if the intervention proves to be effective, the pragmatic nature of the intervention, with the exercise conducted within local community-based health and fitness centres and dietary protein increased through the use of lean red meat at an intake equivalent to the current Australian dietary guidelines of 3–4 serves per week, should ensure that the program can be easily implemented and adopted and is applicable in real life.

Another strength of the study is that our secondary outcomes will provide a unique opportunity to: 1) evaluate the effects of the intervention on neural plasticity, and 2) identify potential biological determinants of exercise and protein-induced changes in cognitive function (and skeletal muscle health) in older adults. Specifically, this study will be one of the first to determine whether combining exercise with increased dietary protein (lean red meat) can have a positive effect on a range of neurobiological markers, including various circulating growth and neurotrophic factors (e.g., IGF-1, BDNF, VEGF) and systemic inflammatory cytokines in older adults, and whether any changes in these biological determinants in response to the intervention are associated with any changes in cognitive function and neural plasticity.

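### The adverse-event outcome counts only events judged intervention-related that change the programme or the diet, so it cannot give an unbiased all-cause comparison of clinical events between arms

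*Protocol article*

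**What the plan says.** All references are to the protocol article.

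- **Exercise events (Adverse events).** "An adverse event will be defined as an intervention-related event resulting in absence from, or modification to, the exercise program". At the end of each 4-week period, "participants will be required to document any exercise-related adverse events including any injuries related to the exercise program".
- **Diet events (same section).** "Diet-related adverse events (intervention-related events resulting in modification of dietary instructions) will be collected via a telephone administered questionnaire every 8-weeks".
- **Status of the outcome.** Secondary outcome measures ends its list with "memory, mood, anxiety/depression, health-related quality of life and adverse events". Table 1 instead places adverse events among the additional measures, with "Exercise cards and adverse events form" as the source and monthly collection.
- **Blinding (Randomisation and blinding).** "Neither the participants nor research staff involved in the testing will be blinded to the allocation, but those analysing the data will be blinded".
- **Use of the result (Discussion).** The trial is to evaluate whether the combination "is a safe and effective strategy to enhance muscle mass, size and strength and cognitive function in community-dwelling older adults". The closing summary anticipates direct evidence that red meat within the guideline limit is safe, and expects no harm to cardiovascular outcomes or kidney function.

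**The concern.** An adverse-event definition normally records what happened and leaves cause and consequence to be judged afterwards. Here both judgements are conditions of entry. An event that nobody links to the intervention, or that leaves attendance and dietary instructions unchanged, does not meet the definition and need not be recorded.

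The strength of a randomised comparison of harms is that it does not depend on anyone's view of cause: all events are counted and the arms are compared. Filtering on perceived cause gives that up, and in an open-label trial the perception can differ by arm. Blinded analysts cannot restore events that were never written down.

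At stake are a listed secondary outcome and the word *safe* in the Discussion. The primary muscle and cognition analyses are not affected.

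**Working it through.** The article states no adverse-event rate, safety margin or power for safety, so there is no figure to reproduce. The check is mainly textual. An illustration on assumed rates follows.

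**1. Two conditions for each type of event.**

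| Event type | Condition 1 | Condition 2 | How collected |
|---|---|---|---|
| Exercise | intervention-related | absence from or change to the programme | participant record, every 4 weeks |
| Diet | intervention-related | change to dietary instructions | telephone questionnaire, every 8 weeks |

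The article describes no all-cause collection of adverse events.

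**2. Where the arms can differ.** The Exercise program section gives both arms the same training, so attribution to exercise has less reason to differ by arm. The randomised contrast is diet. The meat arm eats about 160 g of cooked meat on each training day (Lean red meat). The control arm eats at least one serving of about half a cup of rice or pasta, or a potato, with advice to favour carbohydrate and take smaller serves of protein foods (Carbohydrate control). A complaint that prompts a change to one set of instructions need not prompt a change to the other. Capture can therefore differ by arm even if every attribution is honest.

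**3. Effect on the comparison.** Let *p* be the true risk and *c* the probability that an event passes both conditions. Then

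observed risk = *p* × *c*

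observed risk ratio = true risk ratio × (*c* in arm A / *c* in arm B).

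All values of *p* and *c* below are assumptions; the documents give neither. Power is for a two-sided 5% test of two proportions with 152 / 2 = 76 per arm, using the total in the Abstract and Participants sections. The Sample size calculations section speaks of 152 in each group. The risk ratios do not depend on which is meant, but the power figures do.

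| True risk A, B | Capture A, B | Observed risk A, B | Ratio: true → observed | Chance of P<0.05 |
|---|---|---|---|---|
| 30%, 30% | 60%, 30% | 18%, 9% | 1.0 → 2.0 | 37% |
| 30%, 30% | 30%, 60% | 9%, 18% | 1.0 → 0.5 | 37% |
| 40%, 20% | 30%, 60% | 12%, 12% | 2.0 → 1.0 | – |
| 40%, 20% | 60%, 30% | 24%, 6% | 2.0 → 4.0 | 88% |
| 40%, 20% | 100%, 100% | 40%, 20% | 2.0 → 2.0 | 77% |
| 40%, 20% | 50%, 50% | 20%, 10% | 2.0 → 2.0 | 41% |
| 40%, 20% | 25%, 25% | 10%, 5% | 2.0 → 2.0 | 21% |

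Unequal capture can create a difference, hide one or exaggerate one, and it can count against the meat arm as easily as for it. Equal capture keeps the ratio but loses power.

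**4. What escapes the filter.** These are collected in both arms whatever anyone thinks of cause:

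- lipids, hs-CRP, creatinine, urea and eGFR at baseline, 12 and 24 weeks (Biochemical, hormonal and inflammatory markers);
- blood pressure at baseline and week 24 (Blood pressure; Table 1);
- new or altered medication, by monthly telephone call, and a lifestyle questionnaire covering illness, falls and fractures (Health and medical history and medication use).

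They bear directly on the cardiovascular and kidney expectation in the Discussion. They are not a comparison of clinical events in general.

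**The case against.** The strongest reply is that the trial measures harm in other ways. A reader might infer from the definition that harms cannot be compared between arms at all, or that no safety statement is supportable. The documents do not bear that out. Unfiltered laboratory, blood pressure and medication data are taken in both arms and match the specific safety expectation in the Discussion. Session attendance is also logged whatever the reason for absence (Compliance). Even the filtered events are sought in both arms and still say something about the rate of related events that change the programme or diet. It would be wrong to say that they exclude nothing. This part of the reply stands, and it limits the point to the adverse-event outcome and to the general word *safe*.

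A reader might also see a conflict between monthly collection in Table 1 and the 8-week interval for diet events. There is none: the table row names the exercise cards and the event form, while diet events come from a separate telephone questionnaire. At most, the table omits that questionnaire.

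Three further replies have some force.

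- The article does not say who judges relatedness, so differential attribution is a risk and not a demonstrated fact. But participants, who document the exercise events, know their allocation, and nothing describes a blinded assessor.
- Adverse events are secondary in one place and an additional measure in another. This lowers their weight but does not change the definition.
- An article may leave serious-event reporting to the full protocol, and its silence on that is no fault. The definition, however, is stated here.

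**Conclusion.** The point holds in a limited form. As written, the adverse-event outcome is filtered by open-label attribution and by consequence, so it cannot give an unbiased all-cause comparison of clinical events between arms. The direction of any bias is unknown. Its size cannot be derived from the article: it depends on the ratio of capture probabilities between arms, and the illustration shows only that a twofold difference in capture would double or halve the observed risk ratio.

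The cardiovascular and kidney expectation has its own unfiltered data and is not undermined by the definition. The general description of the strategy or dose as safe goes beyond what those data and the filtered event count can support. The issue is worth correcting because the remedy is cheap, but it touches a secondary outcome and the safety conclusion only.

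**What to change.** **Adverse events section.** Record all adverse and serious adverse events in both arms, whatever their cause or consequence, using the monthly forms and monthly calls that already exist. Hold relatedness, and change to the programme or diet, as separate fields. Compare all-cause events and related events by arm. The present definition can still be recovered as a subset.

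**Events already missed.** The Trial status section says participants have already started, so some events may have gone unrecorded. For that part of the trial, limit the safety conclusion to the measured laboratory and blood pressure outcomes and to related events that changed the programme or diet. Recruitment is staggered in two cohorts over two years (Recruitment), so later participants can still be covered in full.

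**Discussion.** Word the safety statement to match.

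**Cost.** Slightly more data entry, and a change of form wording during the trial, whose date must be recorded so that events collected under the two definitions are not pooled as if alike.
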